## Abstract

**Background:**

Cardiovascular diseases cause the death of 17.5 million people every year. Cardiac catheterization is an invasive diagnostic exam that allows treatment followed by the examination and can cause some complications such as pain. From this perspective, music has alleviated suffering and promoted pain relief for patients. This study aims to evaluate the effectiveness of music therapy to relieve pain in adults and older adults during femoral arterial sheath removal after cardiac catheterization.

**Methods:**

This is a randomized controlled clinical trial, with two arms and a single-blind design to be carried out with 68 patients equally allocated into control and experimental groups. The intervention will be applied with the use of headphones without any musical transmission in the control group or with the patient’s musical preference in the experimental group with sound intensity of 60 dB. These patients will be evaluated in three moments: immediately before, during and 15 min after the painful procedure. The primary outcome includes reduction of pain intensity verified by the Visual Analogue Scale and the secondary outcome corresponds to improvement of vital signs and vocal and facial pain expressions.

**Discussion:**

This study will allow by testing a non-pharmacological strategy to relieve pain during femoral sheath removal after cardiac catheterization, having its parameters evaluated at three moments: immediately before (30 min), during the procedure and 15 min after the painful procedure. It also enables the use of a low-cost, potentially effective resource that makes nursing care more humanized by improving user satisfaction with the service provided, in addition to reducing the need for post-procedure analgesics.

**Trial registration:**

This study is registered on the Brazilian Clinical Trials Registry (REBEC) platform under number RBR-3t3qwp7 (05/04/2022) and was approved by the Research Ethics Committee of the Federal University of Rio Grande do Norte under CAAE 52,586,521.8.0000.5537 (11/11/2021).

## Background

Cardiovascular diseases (CVD) are the leading cause of death worldwide, causing the death of 17.5 million people every year according to the World Health Organization (WHO) [1]. As one of the greatest public health problems, acute coronary syndrome stands out through the occurrence of Acute Myocardial Infarction—with or without ST segment elevation—and stable angina, which affects about 85.6 million adults with at least one type of the disease, only in the United States [2].

Acute coronary diseases are diagnosed through electrocardiogram examination, analysis of clinical signs and cardiac enzymes and are confirmed by hemodynamic evaluation, cardiac catheterization. Also known as coronary angiography or cine-angiography, cardiac catheterization is an invasive diagnostic test performed to analyze coronary vessels or heart muscles through the insertion of catheters by arterial puncture in the arms or legs to reach heart chambers. Thus, this therapeutic approach provides accuracy in anatomical and functional visualization, which allows the treatment to be carried out followed by the examination [3].

It was observed that the establishment of more elaborate processes in hemodynamics laboratories enables the appearance of complications in patients undergoing endovascular procedures. Among them, those that stand out most frequently are pseudoaneurysms, hematomas, distal embolization, bleeding at the insertion site, and arterial thrombolysis [4]. However, acute pain is the most recurrent complaint of patients undergoing endovascular procedures, either in the puncture site, in the back, thoracic and lumbar region, or even headache. The painful phenomenon may be associated with limb immobilization, bed restriction, or due to puncture-related vascular trauma or complications during the procedure [5].

Pain is related to both a sensory and an emotional experience [6]. In this sense, many tools have been used in the scientific and clinical environment to measure pain, considering that it is considered the fifth vital sign by the American Pain Society and its evaluation should be mandatory [7].

The measurement of this phenomenon can be performed through the use of scales to assess pain in adults, namely: non-verbal pain scale (NVPS), critical care pain observation tool (CPOT), behavioral pain scale (BPS), behavioral pain assessment tool (BPAT), pain assessment tool (PAT) and COVERS scale, behavioral pain indicators scale (ESCID) [8]. The Visual Analogue Scale (VAS) is understood as the simplest and most universal scale that enables the application of a self-assessment method for the patient from the absence of pain to unbearable pain, ranging from zero to ten, from one to three being considered mild pain, four to seven moderate and eight to ten severe pain [9].

It is up to the nurse to assist in pain management throughout the nursing process, using to assess pain, pharmacological and non-pharmacological therapies and the control of patient responses. Thus, the implementation of non-pharmacological strategies is considered as complementary, helping to relax, improve sleep patterns and relieve pain [10]. Thus, nursing has used Integrative and Complementary Practices in Health (ICPS) as a new method of patient care for pain relief, namely: acupuncture, aromatherapy, cryotherapy, phytotherapy, hydrotherapy, homeopathy, massage, meditation, music therapy, reiki and therapeutic touch [11].

The use of music therapy also collaborates in the therapeutic treatment with physiological effects related to changes in metabolism, regulation of respiratory rate, release of adrenaline, variations in Blood Pressure (BP), reduction of fatigue and increase in sensory stimuli. Therefore, it is an accessible therapeutic tool, easy to use, with no side effects, allowing wide use in different therapeutic scenarios [12]. From this perspective, interventions with music alleviate suffering and pain in patients by promoting positive auditory stimuli that camouflage adverse sounds, improve emotional health and induce a feeling of hope and well-being during treatment [13].

Similarly, a retrospective study carried out with 99 patients in China sought to evaluate the effects of music on anxiety, pain and depression of patients after coronary artery bypass graft surgery. The research describes significant reduction in the numerical pain scale (*p* < 0.05) after 30 min of musical intervention, when compared with results using the same scale before intervention and when comparing the experimental group with the other study groups: rest without music and standard service care [14].

In addition to these important variables, a quasi-randomized Controlled Clinical Trial described the effects of natural sounds on anxiety and physiological parameters such as systolic, diastolic and mean blood pressure, Heart Rate (HR) and oxygen saturation in 130 subjects undergoing coronary angiography. Positive and statistically significant results (*p* < 0.05) have been reported in reducing anxiety and the physiological parameters associated with it, and it is therefore considered an effective intervention, with no side effects [15].

Given the above, the questions are: is music effective in relieving pain during arterial sheath removal after cardiac catheterization via the femoral route? What physiological changes are promoted by the use of this strategy? Does the use of this technology influence the outcome of the Visual Analogue Scale (VAS) of pain in these patients?

### Objective

To evaluate the effectiveness of music therapy to relieve pain in adults and older adults during femoral arterial sheath removal after cardiac catheterization.

## Methods/design

This study is registered on the Brazilian Clinical Trials Registry (REBEC) platform under number RBR-3t3qwp7 (05/04/2022) and was approved by the Research Ethics Committee of the Federal University of Rio Grande do Norte under CAAE 52,586,521.8.0000.5537 (11/11/2021). This protocol complies with the Standard Protocol Items for Randomized Trials (SPIRIT) [16].

### Trial design

This is a protocol of a Randomized Controlled Clinical Trial (RCT) with two arms and single-blind intervention design, which compares the effects of music therapy to relieve pain in adults and older adults during femoral arterial sheath removal after cardiac catheterization with standard interventions already used by the service for this same procedure.

### Population

The population will be composed of individuals who will undergo cardiac catheterization at the largest hemodynamics service of the state of Rio Grande do Norte, located in Natal, state of Rio Grande do Norte, Brazil, with the need to remove the arterial sheath via the femoral route. The sample will be random and simple probability.

### Eligibility and recruitment criteria

The following inclusion criteria will be adopted: patients aged 18 years or older admitted to hemodynamics for elective cardiac catheterization, with the need to remove the arterial sheath via the femoral route. Those who do not like music, who have previously undergone the procedure, those with chronic pain, diagnosis of arboviruses, fibromyalgia, previous analgesia, individuals with neurological and/or cognitive problem that compromise the understanding and use of the scale and individuals with hearing impairment will be excluded. Figure 1 shows the study flow.

**Fig. 1 Fig1:**
[figure not shown]
Flow diagram of survey participants adapted from CONSORT (2010) [17]

#### Interventions

The Control Group (CG) will be composed of 34 patients allocated in a simple random way with clinical indication of performing cardiac catheterization. These patients will receive the standard care already adopted by the service, in addition to the application of headphones without any musical transmission for the removal of the arterial sheath via the femoral route in a timely manner and will remain with the headphones for 15 min after the end of the painful procedure.

The Experimental Group (EG), in turn, will be composed of 34 patients allocated in this group in a simple random way, who will receive the same care as the previously mentioned group, in addition to the application of headphones which will transmit the patient's musical preference during the performance of the painful procedure up to 15 min after its completion. The headphones will be used in a complementary way and not as a substitute for the care already adopted by the service.

#### Questionnaire

At first, the principal researcher will apply a form previously prepared with participants of both groups containing the following sociodemographic data: date of birth, age, sex, color, marital status, schooling, profession, family income and musical preference.

At this time, the initial part of the second previously prepared form will also be applied, containing the following clinical data: comorbidities, reason for performing cardiac catheterization and medications in use. After completing this part, blood pressure, heart and respiratory rate vital signs will be measured, as well as information regarding oxygen saturation, presence or absence of bodily signs and symptoms of pain such as sweating, pallor, vocal or face expression or pain. These data will be recorded in the second previously prepared form and repeated during the intervention and 15 min after the end of the painful procedure.

This second form also contains information regarding the French number of the arterial sheath, the professional responsible for removing it, if there were complications during the painful procedure and what these complications were; if there were complications after the procedure and what these complications were; how long the arterial compression lasted after the intervention; if there was need for analgesia after the procedure and the time to receive the hemodynamic discharge. Finally, the Visual Analog Pain Scale will be applied to identify pain intensity.

## Results

### Primary outcome

The primary outcome expected is reduction in pain intensity through the Visual Analogue Scale (VAS) [17] and reduction in the following physiological parameters: blood pressure, heart and respiratory rate, in addition to the improvement of oxygen saturation levels through the application of the patient's musical preference using headphones during the removal of the arterial sheath via the femoral route after cardiac catheterization.

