### Secondary outcome

The secondary outcome expected is absence of bodily signs and symptoms of pain verified through the absence of the following parameters: sweating, pallor and facial expression of pain, in addition to reduction of the intensity levels of vocal expressions of pain, namely: screaming, crying, groaning, verbal report of pain or their absence through the application of the patient's musical preference using headphones during the removal of the arterial sheath via the femoral route after cardiac catheterization.

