### Sample size

The sample size calculation was performed using the G Power software, version 3.1.9.2, with Cohen effect of 0.50, test power of 0.80 and significance level of 5%, establishing N of 34 patients per group, experimental and control, totaling 68 patients.

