#### Data extraction and statistical analysis

Data will be described in a database previously built in Microsoft Excel and exported to the Statistical Package for Social Science Version 18.0 software (SPSS Version 20.0), where descriptive and inferential analyses will be performed. The Kolmogorov–Smirnov test will be used to assess the normality of variables. For the evaluation of variables, the Chi-square (χ^2^) or Fisher's Test will also be used. Other tests that may be necessary will also be adopted. Results will be presented through tables, charts and figures, adopting significance level of 5% (*p* = 0.05).

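### Vital signs are a secondary outcome in the Abstract but part of the primary outcome in the Primary outcome section, and nothing says whether any or all components must succeed

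*Protocol article*

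**What the plan says.** The article defines its outcomes twice.

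- **Abstract, Methods.** On the primary outcome: "The primary outcome includes reduction of pain intensity verified by the Visual Analogue Scale". On the rest: "the secondary outcome corresponds to improvement of vital signs and vocal and facial pain expressions".
- **Results, Primary outcome.** After pain on the VAS, the sentence continues "and reduction in the following physiological parameters: blood pressure, heart and respiratory rate, in addition to the improvement of oxygen saturation levels". This makes five named measures: VAS pain, blood pressure, heart rate, respiratory rate and oxygen saturation.
- **Results, Secondary outcome.** "The secondary outcome expected is absence of bodily signs and symptoms of pain verified through the absence of the following parameters"; the list that follows covers sweating, pallor, facial expression and vocal expressions. No vital sign appears.

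Two other sections bear on how the outcomes would be judged. Sample size gives one calculation, "with Cohen effect of 0.50, test power of 0.80 and significance level of 5" per cent, without naming the endpoint. Data extraction and statistical analysis gives one general threshold, "adopting significance level of 5" per cent, without assigning it to any outcome. No section states a success rule for a primary outcome with several components.

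**The concern.** The primary outcome decides whether the trial is reported as positive. Here either published definition could be cited once the results are known. The stated objective is pain relief, and the Background asks about physiological changes as a separate question. Under the longer definition, a change in one vital sign could be presented as a result on the primary outcome even if pain did not differ.

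The longer definition also cannot be interpreted as it stands. With five measures and no rule, a reader cannot tell whether the trial runs a raised risk of a false claim (any one suffices) or a raised risk of missing a real effect (all required).

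**Working it through.** **1. The two definitions side by side**

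| Measure | Abstract | Outcome sections |
|---|---|---|
| VAS pain | primary | primary |
| Blood pressure, heart rate, respiratory rate | secondary (as vital signs) | primary |
| Oxygen saturation | secondary, if counted as a vital sign | primary |
| Facial and vocal signs of pain | secondary | secondary |
| Sweating, pallor | not named | secondary |

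The second row cannot be reconciled, and the third adds to the conflict on the ordinary reading.

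**2. The plan's own figures**

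The article states no overall false-positive rate; its only related figure is the 5% level. The sample size is 34 per group from an effect of 0.50, power 0.80 and 5%. A two-sample t-test with those inputs needs 63.8, so 64 per group, two-sided (50.2, so 51, one-sided). With 34 per group, power for one endpoint is 53% two-sided or 65% one-sided. Among the designs tried, 34 appears only as a total: a paired or one-sample t-test (33.4) or a two-group analysis of variance with f = 0.5 (33.4). That shortfall is a separate matter. It is noted because it affects any power figure below.

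**3. If any one result counts, each tested at an unadjusted 5%**

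For k independent tests the chance of at least one false positive is 1 − (1 − 0.05)^k.

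- k = 5 (the measures named): 1 − 0.95^5 = 1 − 0.774 = 22.6%. Upper bound 5 × 5% = 25%.
- k = 6 (systolic and diastolic pressure tested separately): 1 − 0.95^6 = 1 − 0.735 = 26.5%. Upper bound 30%.

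The article gives no correlation between the measures, so a range is needed. Simulation of normal test statistics with a common correlation (2 million draws, two-sided 5% each) gives:

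| Common correlation (assumed) | Five tests | Six tests |
|---|---|---|
| 0.3 | 20.9% | 24.2% |
| 0.4 | 19.7% | 22.6% |
| 0.5 | 18.3% | 20.8% |
| 0.7 | 14.9% | 16.4% |
| 0.9 | 10.2% | 10.9% |

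**4. If all results are required**

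The false-positive rate is then at most 5% with no adjustment. Power is the chance that every test succeeds, and it cannot exceed that of the weakest single test. If each of five endpoints had the planned 80% power and they were independent, joint power would be 0.80^5 = 33% (six: 0.80^6 = 26%). Positive correlation raises this towards, but not above, 80%. These figures assume adequate power on every measure, which the article does not claim.

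**5. Time points**

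Vital signs are recorded at three moments. Table 1 places the headphones only at P2 and F1, so P1 is a baseline and not a test of effect. Two moments remain for the vital signs, and the Primary outcome section names neither. Table 1 lists VAS at F1 only. Testing vital signs at both moments would add tests; this is not included in the sizes above.

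**The case against.** The strongest reply is that the longer definition joins its measures by a conjunction. Read literally, all must improve, and then nothing is inflated. A success rule and any multiplicity adjustment are also commonly left to an analysis plan, which is not shown, and an article condenses the full protocol. The 5% level is stated generally; the article does not say that each component will be tested at 5% without adjustment. The registry entry, also not shown, may already fix a single primary outcome. Finally, the Abstract says that the primary outcome includes VAS pain, which is not quite the same as VAS alone.

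Much of this stands, and it limits what can be claimed. A reader might infer that the trial's false-positive rate is above 20%. The article does not support that as a fact: it needs an any-one-suffices rule and unadjusted tests, neither of which is stated, and for the five named measures it also needs a correlation below about 0.4. A reader might likewise infer that an all-required rule leaves almost no power, about 2% to 16% for six measures with 34 per group at correlations from 0 to 0.5. That assumes an effect of 0.50 on every measure, and it partly reflects the separate sample-size shortfall.

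The reply does not remove the contradiction. The Abstract expressly assigns vital signs to the secondary outcome, so the looser verb does not help. Condensation explains omitted detail, not the same measures being given two different ranks.

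**Conclusion.** The contradiction is established from the text alone: vital signs are secondary in the Abstract, primary in the Primary outcome section and absent from the Secondary outcome section. No section says whether any or all of the components must succeed.

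The size is conditional. Under an any-one-suffices rule with unadjusted 5% tests, the false-positive rate runs from about 10% (five tests, correlation 0.9) to about 27% (six independent tests), against a nominal 5%. Under an all-required rule there is no inflation, but power is well below that of one endpoint. The article does not fix which case applies. The primary outcome should therefore be settled before any outcome data are examined.

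**What to change.** Rewrite the Primary outcome section to agree with the Abstract and the Objective: VAS pain at one named time point, consistent with Table 1 (which lists VAS only at F1), as the sole primary outcome, tested at two-sided 5%. List blood pressure, heart rate, respiratory rate and oxygen saturation as secondary, supportive outcomes. Check that the registry entry says the same, and amend whichever is out of line.

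With one primary test the false-positive rate for the main claim returns to 5%, and no multiplicity adjustment is needed for it. Whether to adjust among the secondary outcomes is a matter of preference.

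The cost is a change of wording and possibly a registry update. The downside is small: vital-sign results lose primary, confirmatory status. This change does not resolve the sample-size shortfall noted in the working.

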### Secondary outcome

The secondary outcome expected is absence of bodily signs and symptoms of pain verified through the absence of the following parameters: sweating, pallor and facial expression of pain, in addition to reduction of the intensity levels of vocal expressions of pain, namely: screaming, crying, groaning, verbal report of pain or their absence through the application of the patient's musical preference using headphones during the removal of the arterial sheath via the femoral route after cardiac catheterization.

### Screening

Immediately before carrying out the procedure, the first researcher will recruit the possible subjects and explain the main study objective, the possible risks and benefits involved in the study and emphasize that he/she may withdraw from participating in the research at any stage of it.

If there is affirmative answer, this first researcher will apply the inclusion and exclusion criteria to select the individuals who will compose the sample. Then, they will be asked to read and sign the Free and Informed Consent Form (FICF) to guarantee their participation in the study.

### Follow-up

Table 1 describes the adapted SPIRIT schedule with appropriate enrollment times, interventions and participant assessments.

**Table 1 Tab1:** Standard protocol items: adapted recommendations for interventional trials (SPIRIT) schedule: enrollment, interventions and evaluations

STUDY PERIOD						
	**Enrolment**	**Baseline**	**Post-allocation: Allocation, Interventions, Follow-up**			
**TIMEPOINT**			**Allocation**	**P1**	**P2**	**Follow-up (F1)**
**ENROLMENT:**						
Eligibility criteria	X					
Recruitment	X					
Initial assessment	X					
Informed consent	X					
Allocation			X			
**INTERVENTIONS:**						
* Headphones* with no musical transmission (Control group)					X	X
* Headphones* with the patient’s musical preference (Experimental group)					X	X
